## Abstract

**Background:**

Classic neuraxial techniques, such as thoracic epidural anesthesia, or alternative approaches like the paravertebral block, are not indicated in cardiac surgery due to increased bleeding risk. To provide satisfactory analgesia without the need for excessive opioid use, novel ultrasound techniques gained popularity and are of growing interest. The pectoralis nerve block II (PECS II) has been shown to provide good postoperative analgesia in modified radical mastectomy and might also be suitable for minimally invasive cardiac surgery.

**Methods:**

In a single center, prospective, triple-blinded, two-group randomized trial, 60 patients undergoing elective, unilateral minimal invasive cardiac surgery will be randomized to receive a PECS II with 30 ml of ropivacaine 0.5% (intervention group) or sodium chloride 0.9% (placebo group). The primary outcome parameter is the overall opioid demand given as intravenous morphine milligram equivalents (MME) during the first 24 h after extubation. Secondary endpoints are the visual analog scale (VAS) 2, 4, 6, 8, 12, and 24 h after extubation, the Overall Benefit of Analgesia Score (OBAS) after 24 h, the interval until extubation, and intensive care unit (ICU) discharge within 24 h, as well as the length of hospital stay (LOS).

**Discussion:**

This prospective randomized, controlled, and triple-blinded trial aims to assess if a PECS II with ropivacaine 0.5% helps to decrease the opioid demand in the first 24 h and increases postoperative pain control after minimally invasive cardiac surgery.

**Trial registration:**

www.clinicaltrialsregister.eu; EudraCT Nr: 2021–005452-11; [name] MD, November 18, 2021.

## Introduction

### Background and rationale {6a}

A multidisciplinary approach in perioperative care is crucial for improving patient recovery after major surgery. The so-called Enhanced Recovery After Surgery (ERAS) is an evidence-based protocol ranging from preoperative patient optimization to intra- and postoperative strategies aiming to improve clinical outcomes and reduce hospital stays. With the introduction of minimally invasive cardiac surgery (MICS) through two or three small thoracotomies, ERAS strategies gained popularity, and recently, ERAS guidelines for cardiac surgery have been presented, emphasizing that critical factors that keep patients hospitalized after major cardiac surgery are among others, perioperative pain, prolonged mechanical ventilation, and immobilization [1–3].

Apart from less invasive surgical techniques, implementing a multimodal concept for pain therapy, including regional anesthesia, is an essential element of ERAS pathways [4]. In patients undergoing major cardiac surgery, the possibilities for neuraxial blocks are limited and controversially discussed due to increased bleeding risk [5].

Ultrasound-guided, interfacial plane blocks represent a relatively new route of transmitting local anesthetics to the space between two fascial layers to provide the blockade of nerves traveling within this plane, leading to analgesia of the chest or abdominal wall. These blocks have already been shown to be relatively easy to perform and to have low complication risks [5, 6].

The pectoral nerves (PECS) II block was initially introduced in 2012 as an extension of the PECS I block (injection of local anesthetic between the pectoralis major and pectoralis minor muscles), involving a second injection in the fascial plane between pectoralis minor and serratus anterior muscles [7, 8]. It targets the pectoral nerves, the intercostal nerves III-VI, the intercostobrachial, and the long thoracic nerve. Compared to systemic opioids, the PECS II block has already been proven to effectively facilitate pain relief to the upper anterior chest wall in patients undergoing modified radical mastectomy [9–11]. Looking at the unilateral right-sided approach of MICS, a PECS II block could be a suitable regional anesthetic technique to improve postoperative analgesia for patients undergoing MICS [5].

Therefore, this prospective, triple-blinded, randomized trial aims to evaluate the efficacy of the PECS II block in patients undergoing unilateral MICS.

### Objectives {7}

The primary objective of this trial is to evaluate the efficacy of the PECS II block in patients undergoing unilateral MICS expressed as the reduction in the overall opioid demand given as intravenous MME during the first 24 h after extubation.

The secondary objective of this trial is to evaluate the effect of the PECS II block in patients undergoing unilateral MICS on the interval until extubation, ICU discharge, data on ICU, length of hospital stay (LOS), the visual analog scale (VAS) at 2, 4, 6, 12, and 24 h after extubation, and the Overall Benefit of Analgesia Score (OBAS) at 24 h after extubation [12].

### Trial design {8}

This is an investigator-initiated single-center prospective, triple-blinded, two-group, randomized trial with two treatment groups.

## Methods: participants, interventions, and outcomes

### Study setting {9}

In this single-center prospective, triple-blinded, two-group, randomized trial, 60 patients will be recruited and randomly assigned to one of the two groups to test the effect of a PECS II block with ropivacaine 0.5% on the postoperative opioid demand (see Consolidated Standards of Reporting Trials flow diagram (CONSORT) [13] in Fig. 1). The scope of this trial is to improve perioperative pain management in patients undergoing minimally invasive cardiac surgery.

**Fig. 1 Fig1:**
[figure not shown]
Trial flow diagram

The primary outcome parameter is the overall opioid demand given as intravenous MME during the first 24 h after extubation.

The secondary outcome variables are the interval until extubation, ICU discharge, data on ICU, length of hospital stay (LOS), the VAS at 2, 4, 6, 12, and 24 h after extubation, and the Overall Benefit of Analgesia Score (OBAS) at 24 h after extubation [12].

This study will be performed in the Innsbruck Medical University Hospital. All participants will be recruited by a medical specialist team (recruiting team) at the Medical University of Innsbruck (MUI) (Investigation Site). All data will be collected by the research team consisting of physicians and healthcare researchers. The study investigators will perform data analysis.

### Eligibility criteria {10}

Adult patient with an American Society of Anesthesiologist (ASA) physical status I-III, aged 18–80 years, scheduled for elective minimal invasive cardiac surgery, e.g., mitral valve procedures, tricuspid valve procedures, myxoma resection, or atrial septal defect repair. All participants will undergo the usual standard medical work-up before, during, and after the procedure according to the ESC/EACTS Guidelines on Valvular Heart Disease [14].

This includes echocardiography, spirometry, carotid artery duplex scan, cardiac MRI, and/or computed tomography, and interviews with the cardiologist, cardiac surgeon, and anesthesiologist.

To be eligible for this study, patients must meet all of the following criteria:Age: 18–80 years.BMI 18–35 kg/m.^2^Informed consent.MICS

The exclusion criteria are as follows:Known allergies to administered drugs.Severe diabetic neuropathy.LV-dysfunction (EF < 30%).Drug-opioid abuse.Patients with chronic pain syndrome.Systemic infection.Psychiatric disorders that lead to alteration in the perception and evaluation of pain.Pregnancy.Anticipated endotracheal intubation > 24 h.eGFR < 30 or chronic renal disease.

### Who will take informed consent? {26a}

Every participant must give written consent before participating in the clinical trial.

An investigator will provide and obtain the informed consent form. Therein, the investigator will thoroughly inform the participant in oral and written form in an understandable manner for the patient about the character, importance, relevance, and consequences of the clinical trial. Before the participant may sign the informed consent form, there will be ample opportunity to consider participation and discuss questions with the investigators. The informed consent file must be signed and dated by the participant and the investigator and stored in the investigator site file. Nevertheless, if the participant decides not to participate any time before the intervention, he will not be included without negative impacts on the procedure.

### Additional consent provisions for collection and use of participant data and biological specimens {26b}

On the consent form, participants will be asked if they agree to the use of their data should they choose to withdraw from the trial. This includes their data being used for analysis as well as any future publications or presentations related to the study. Since this is a monocenter trial, the consent form will not include a section regarding data sharing permissions. This trial does not involve collecting biological specimens for storage. All necessary measures will be taken to protect the privacy and confidentiality of participants. Participants will also be provided with the contact information for the study team in case they have any questions or concerns regarding their participation in the study.

### The explanation for the choice of comparators {6b}

Two groups will be included. The intervention group receives PCS II block with 30 ml of ropivacaine 5 mg/ml, while the control group receives a plane PECS II block with 30 ml of sodium chloride 0.9%. All other medical interventions will be identical.

### Intervention description {11a}

After obtaining written informed consent, all patients will be taught to assess pain using the visual analog scale (VAS; 0–100 mm). According to institutional standards, patients will be fasted for 6 h for solids and 2 h for fluids and receive oral premedication with midazolam 0.05–0.1 mg /kg if requested.

Before the arrival of the patient in the operating room, a study nurse will open an opaque envelope and prepare the study medication (30 ml ropivacaine 0.5% for the intervention group and 30 ml sodium chloride 0.9% for the placebo group) according to the study randomization and hand it to the blinded anesthetist.

Upon arrival at the operating room, standard monitoring (5-channel electrocardiogram, pulse oximetry (SpO_2_), a peripheral vein cannula, an arterial cannula for continuous invasive blood pressure measurement, and near-infrared spectroscopy (NIRS)) will be installed. Then, all patients will be pre-oxygenated for 3 min with oxygen 100% according to international standards. Anesthesia induction will be performed with midazolam 10-–20 mcg/kg, fentanyl 5–8 mcg/kg, propofol 1–3 mg/kg, and rocuronium 1 mg/kg, and the patient airway will be secured by using an endotracheal tube. All patients will receive controlled ventilation (tidal volume 6–8 ml/predicted body weight) to maintain arterial partial pressure of carbon dioxide (pCO_2_) between 35 and 45 mmHg.

A five-lumen central venous catheter will be inserted in the right subclavian or internal jugular vein, depending on the indication of a bicaval extracorporeal venous drainage for cardiopulmonary bypass. Immediately afterward, the ultrasound-guided PECS II block will be performed under aseptic conditions on the right hemithorax using the technique described by Blanco et al. [8].

According to our institutional standards, a trans-esophageal echocardiographic probe will be inserted in all patients to control and assess cardiac function.

All PECS II blocks will be performed under ultrasound guidance by five consultant anesthetists experienced in the technique (*n* > 50) by using a 22 G × 80 mm needle (SonoPlex cannula, Pajunk®, Geisingen, Germany) and a linear array ultrasound (US) probe (FUJIFILM Sono-Site M-Turbo®, 6–13 MHz). At the midclavicular line, the axillary artery and vein are identified. The linear ultrasound probe is moved caudally and laterally to delineate the pectoralis major, pectoralis minor, and serratus muscle at the third intercostal space. Then, the needle is inserted in-plane from cranial medial to caudal lateral in an oblique manner until the tip is visualized between the pectoralis minor and serratus muscle, and 20 ml of the study medication is injected. After that, the information will be removed until it reaches the plane between the pectoralis major and pectoralis minor muscle, and the remaining 10 ml of the study medication will be injected. Heart rate (HR), blood pressure, and SpO_2_ will be noted immediately before the PECS II block is performed and 5 min after.

### Postoperative analgesia regimen

At the end of the surgical procedures, all patients will receive a bolus of piritramide 0.1–0.2 mg/kg and will be transferred to the postoperative ICU ward. Patients will be extubated when extubation criteria are reached (normothermic, fully awakened, spontaneously breathing, hemodynamically stable with moderate vasopressor support, etc.). After extubation, VAS will be recorded by trained medical staff members and then after 2, 4, 6, 8, 12, and 24 h. If VAS exceeds a value of 30 mm at any time, an administration of piritramide will be allowed. The time interval from completing the PECS II block until the first request for opioids (VAS > 30 mm) after extubation is defined as the duration of analgesia. Opioid consumption will be assessed as an intravenous morphine milligram equivalent (MME) dose.

### Criteria for discontinuing or modifying allocated interventions {11b}

We will exclude patients from participating in case of failure to detect the suitable anatomical structures for PECS II.

After PECS II is performed, it is impossible to change the allocated intervention after administration. Subjects are free to leave the study at any time for any reason without consequences. Study discontinuation should be documented in the subject’s medical file and the case report form (CRF). The investigator can withdraw an issue from the study for urgent medical reasons. These may include the following criteria:Anatomical anomalies, limited visualizationAllergic reaction to the study medicationClinical complications (hemodynamic impairment, re-operation, extracorporeal membrane oxygenation (ECMO), etc.) that may lead to prolonged weaning (more than 24 h)

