### Methods in analysis to handle protocol non-adherence and any statistical forms to handle missing data {20c}

#### Per-protocol population

The per-protocol-population will include all patients who received intervention or sham intervention (placebo) and surgery without major protocol deviations. Significant protocol deviations or complications (hemodynamic instability, prolonged intubation, reintubation, bleeding, reoperation) and subsequent failure to obtain primary and secondary outcome data will be documented before the database lock.

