#### Intention-to-treat population

The intention-to-treat population will consist of all patients who were enrolled in the study and gave informed consent, but data is missing due to the abovementioned factors. This population will be analyzed in a separate ITT cohort. In case of withdrawals and missing data, the last observation carried forward (LOCF) procedure will be applied where appropriate.

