### Adverse event reporting and harms {22}

Although serious adverse events are not to be expected, the sponsor and the principal investigator will suspend the study if there is reasonable doubt that the continuation of the survey will compromise the safety and well-being of participants. In this case, the local ethics committee will be informed immediately, and the study will remain suspended pending a favorable decision from the local ethics committee.

Adverse events will be noted, and serious adverse events will also be reported to the local ethics committee.

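### Investigators may withdraw patients from the study after the block because of a possible harm; no treatment is stopped by this, and follow-up of those patients can be cut short

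*Protocol article*

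**What the plan says.** The rule is in the protocol article under Criteria for discontinuing or modifying allocated interventions {11b}: "The investigator can withdraw an issue from the study for urgent medical reasons" (the word issue evidently stands for a patient). Three kinds of reason are given as examples: anatomical difficulty or poor visualisation; an allergic reaction to the study medication; and clinical complications, among them hemodynamic impairment, re-operation and ECMO, that could delay weaning past 24 h. The section also says "After PECS II is performed, it is impossible to change the allocated intervention after administration" and "Study discontinuation should be documented in the subject’s medical file and the case report form (CRF".

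Four other places bear on the rule:

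- Plans to promote participant retention {18b}: investigators undertake to do all they reasonably can to follow each randomised patient for the whole study period.
- Outcomes {12}: the primary outcome is opioid demand in the 24 h after extubation. Time to extubation, ICU discharge and length of stay are secondary outcomes.
- Adverse event reporting and harms {22}: adverse events are noted and serious ones go to the ethics committee. No exception is made for withdrawn patients.
- Per-protocol and intention-to-treat populations {20c}: "The per-protocol-population will include all patients who received intervention or sham intervention (placebo) and surgery without major protocol deviations". The intention-to-treat set is worded as enrolled and consenting patients, "but data is missing due to the abovementioned factors. This population will be analyzed in a separate ITT cohort".

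**The concern.** The section title speaks of discontinuing the intervention, but the rule discontinues the patient's participation in the study. Stopping a drug early can protect a patient who is still receiving it. Here the drug is given once, before surgery, and cannot be taken back. Ending participation after that point changes nothing that the patient receives; it only ends what the trial learns about the patient.

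The patients concerned are those whose course may depend on what was injected. If they leave at the time of the complication, the trial may record that something happened but not how it evolved, and their efficacy outcomes may never be collected. The comparison is then made among patients selected by an event that occurred after randomisation.

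**Working it through.** No event rates are given for allergy, re-operation, ECMO or hemodynamic impairment, so the check is mainly a comparison of sections.

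**1. What withdrawal can achieve.** The block is a single administration of 30 ml at induction. By {11b} the allocation cannot be altered afterwards. Withdrawal for a reason arising after injection therefore stops no study treatment. Its only possible effect is on follow-up.

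**2. What is kept.** The triggering event has already occurred and been recognised. Under {22} it is noted, and reported if serious. Under {11b} the discontinuation is entered in the medical file and the CRF. The per-protocol paragraph adds that complications and "subsequent failure to obtain primary and secondary outcome data will be documented before the database lock".

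**3. What can be lost.**

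- Later adverse events and the resolution of the first one, if participation ends with the withdrawal.
- The whole primary outcome, if withdrawal comes before extubation, because its 24 h window opens only at extubation. Last observation carried forward cannot repair this: no value in the window exists to carry.
- Time to extubation. A stated ground for withdrawal is a complication that may delay weaning past 24 h, so the rule can remove the longest values of a declared secondary outcome because they are expected to be long.
- ICU discharge and length of stay, for the same patients.

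**4. Whether the loss can differ by arm.** The rule is discretionary and sets no threshold. Blinding means that the decision should not depend on known allocation, but the events that prompt it can still differ in frequency. An allergic reaction to the study medication is more plausible with ropivacaine than with sodium chloride 0.9% (a judgement, not a figure from the article).

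**5. Consistency with the retention section.** {18b} promises to follow randomised patients throughout. {11b} lets the investigator end follow-up when a complication arises. The patient's own freedom to leave is stated in both sections and causes no conflict; the investigator's power to withdraw does.

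**6. Scale, for context only.** The plan's sample size reproduces: n = 2(1.96 + 0.842)² / 0.75² = 27.9, so 28 per group with a two-sided 5% test and 80% power. The planned 7% dropout is 0.07 × 60 = 4.2 patients. With d = 0.75 and a two-sided t-test:

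| Patients lost of 60 | Power |
|---|---|
| 0 | 81.5% |
| 4 (about the planned 7%) | 78.7% |
| 8 (assumed) | 75.6% |
| 10 (assumed) | 73.8% |

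The cost in power is modest. The difficulty is which patients leave, and these figures say nothing about the resulting bias.

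**The case against.** The strongest reply is that withdrawal from a study is not deletion from its records. That is correct, and it limits the point. A reader might infer that harms of the block vanish from the safety record. The article does not support this: {22} has no exception for withdrawn patients, {11b} requires documentation, a study nurse reviews patient files {11c}, and CRF entries are verified against source documents {23}.

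Two related inferences also fail. A reader might conclude that all the withdrawal events are classed as protocol deviations. The per-protocol paragraph says "Significant protocol deviations or complications (hemodynamic instability, prolonged intubation, reintubation, bleeding, reoperation": it names complications alongside deviations, and mentions neither allergy nor ECMO. A reader might also object that no safety population is defined, but a condensed article may leave that to the full protocol or the analysis plan. Nor need the clause "Although serious adverse events are not to be expected" be struck out; it opens a commitment to suspend the trial if participant safety is in reasonable doubt.

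It can further be said that the rule is permissive, that complications count only if they may prolong weaning, and that a patient still ventilated cannot give a pain score. All of this is true. Some outcomes will be unobtainable in such patients, but that is a reason to record them as missing with the cause. It is no reason to end collection of those that remain available, such as time to extubation, length of stay and adverse events.

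What remains unanswered is that the article nowhere says collection continues after an investigator's withdrawal, while it does state a rule whose only effect can be to end it.

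**Conclusion.** The point holds in a limited form. The stated rule lets investigators end study participation after injection because of events that may be consequences of treatment, protects no patient by doing so, and conflicts with the retention section. The triggering event should still be recorded. The later course and the outcomes can be lost, in patients selected after randomisation and possibly unevenly by arm.

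The number affected and the direction of any bias are unknown. The conclusion rests on one reading: that withdrawal from the study ends data collection. If the full protocol states that collection continues after such a withdrawal, the remaining problem is one of wording.

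**What to change.** - In {11b}, limit withdrawal from the study after injection to withdrawal of consent by the patient.
- State that patients with an allergic reaction or a complication stay in follow-up, with outcomes and adverse events taken from the routine record as far as they can be obtained.
- Include these patients when harms are reported by arm.
- Reconcile {11b} with {18b} so that both say the same about follow-up.

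The change concerns data collection only and leaves clinical care as it is. Healthcare data already come from the electronic patient file {18a}, and a study nurse already reviews the files {11c}, so no extra staff or procedure is needed. The cost is slightly more data collection and adverse event reporting, and a formal amendment if the change is judged substantial under {25}.

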### Outcomes {12}

The primary outcome parameter is the overall opioid demand given as intravenous MME during the first 24 h after extubation.

Secondary outcome variables are the interval until extubation, ICU discharge, data collected in the ICU, length of hospital stay, the VAS at 2, 4, 6, 12, and 24 h after extubation, and the Overall Benefit of Analgesia Score (OBAS) at 24 h after extubation [12].

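### Patients can be withdrawn on the expected value of a secondary outcome, time to extubation, which leaves that comparison open to selection bias of unknown direction

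*Protocol article*

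**What the plan says.** Under Criteria for discontinuing or modifying allocated interventions {11b}, the protocol article states: "The investigator can withdraw an issue from the study for urgent medical reasons". The examples include clinical complications such as hemodynamic impairment, re-operation and ECMO "that may lead to prolonged weaning (more than 24 h"). The same section says that the allocation cannot be changed once the block is given, so this withdrawal can fall after randomisation and treatment.

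Outcomes {12} reads: "Secondary outcome variables are the interval until extubation, ICU discharge, data collected in the ICU, length of hospital stay". The Abstract, Objectives {7}, Study setting {9} and Discussion also list time to extubation.

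The per-protocol population consists of "all patients who received intervention or sham intervention (placebo) and surgery without major protocol deviations". The next sentence of that section names "hemodynamic instability, prolonged intubation, reintubation, bleeding, reoperation" as significant deviations or complications, to be documented, together with the resulting failure to obtain outcome data, before database lock.

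The intention-to-treat population is worded as "all patients who were enrolled in the study and gave informed consent, but data is missing due to the abovementioned factors". It is to be analysed as a separate cohort, with LOCF where appropriate.

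**The concern.** Withdrawal and analysis-set rules that act after randomisation should not depend on the value of an outcome being compared. Here the withdrawal ground refers to weaning time, and one listed deviation or complication is a long intubation, while time to extubation is a declared outcome. If these patients drop out of the comparison, the two arms are no longer the randomised groups for that outcome, and the missing values come mainly from the upper tail. ICU discharge and length of stay are affected in part, since a long wean tends to delay both. At stake is whether a reported difference in extubation time, or its absence, can be attributed to the block.

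**Working it through.** **1. Can the stated rules restore a withdrawn patient?**
- Intention-to-treat set: as worded, it holds patients with missing data as a separate cohort. It is not defined as all randomised patients.
- LOCF: it needs an earlier value of the same variable. Time to extubation is measured once, so a patient not yet extubated has none.
- Statistical methods {20a}: t-test, χ2 or non-parametric equivalents, repeated-measures ANOVA, GEE and regression. As described, none handles a patient whose extubation time is unknown or censored.
- Eligibility criteria {10}: the exclusion for anticipated intubation over 24 h applies before randomisation and does no harm. The {11b} rule uses the same threshold afterwards.

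**2. The plan's own figures.** The sample size concerns opioid demand, not extubation. It reproduces by the normal approximation: 2 × (1.960 + 0.842)² / 0.75² = 27.9, so 28 per group. Enrolling 60 for 56 leaves room for 4 losses of any kind (4/60 = 6.7%). No distribution of extubation times is given, so steps 3 and 4 rest on assumptions.

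**3. If the block shortens all times proportionally.** Assume log-normal times with control median m and log SD s, and block times multiplied by r. With k = ln(24/m)/s, the full mean is m·exp(s²/2), and the mean after deleting values over 24 h is m·exp(s²/2)·Φ(k − s)/Φ(k). For the block arm, replace m by r·m.

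Example, m = 8 h, s = 0.8, r = 0.8:
- Control: k = 1.373; full mean 11.017 h; after deletion 11.017 × 0.7167/0.9151 = 8.63 h.
- Block: k = 1.652; full mean 8.814 h; after deletion 8.814 × 0.8029/0.9507 = 7.44 h.
- The difference falls from 2.20 h to 1.19 h, a loss of 46%.

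| m (h) | s | r | over 24 h, control / block | difference, all (h) | after deletion (h) | lost |
|---|---|---|---|---|---|---|
| 6 | 0.5 | 0.8 | 0.3% / 0.1% | 1.360 | 1.315 | 3% |
| 10 | 0.5 | 0.8 | 4.0% / 1.4% | 2.27 | 1.78 | 22% |
| 6 | 0.8 | 0.7 | 4.2% / 1.5% | 2.48 | 1.73 | 30% |
| 8 | 0.8 | 0.8 | 8.5% / 4.9% | 2.20 | 1.19 | 46% |
| 8 | 1.0 | 0.8 | 13.6% / 9.3% | 2.64 | 0.95 | 64% |

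Patients removed at 30 per arm: 30 × (0.003 + 0.001) = 0.1 in the first row, 30 × (0.085 + 0.049) = 4.0 in the fourth, 30 × (0.136 + 0.093) = 6.9 in the last.

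**4. If the long weans are complications that the block does not shorten.** Assume uncomplicated times with control median 6 h, s = 0.5, r = 0.8, capped at 24 h (means 6.79 h and 5.44 h). Complicated times are uniform from 24 to 96 h (mean 60 h). Removing the complicated patients always leaves 6.79 − 5.44 = 1.35 h.
- 7% in both arms: (0.93 × 6.79 + 0.07 × 60) − (0.93 × 5.44 + 0.07 × 60) = 10.51 − 9.26 = 1.26 h (rounding aside). Removal raises it slightly to 1.35 h. By simulation the standardised difference rises from 0.08 to 0.42.
- 3% control, 7% block: (0.97 × 6.79 + 0.03 × 60) − 9.26 = 8.39 − 9.26 = −0.87 h, a harm. Removal shows a benefit of 1.35 h.
- 7% control, 3% block: 10.51 − (0.97 × 5.44 + 0.03 × 60) = 10.51 − 7.08 = 3.44 h (rounding aside). Removal shrinks it to 1.35 h.

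**The case against.** The other side has a good case on how far this goes. Withdrawal is discretionary and for urgent medical reasons, and it is decided by investigators blinded to arm. It attaches to complications that are mainly circulatory or surgical, not to slow weaning as such. Prolonged intubation appears under deviations or complications to be documented; that it excludes a patient from the per-protocol set is the natural reading, but it is not stated outright. No section says that extubation times of withdrawn patients are discarded. The article promises reasonable efforts at follow-up {18b}, takes healthcare data from the electronic patient file {18a}, and asks participants who choose to withdraw whether their data may be used {26b}. The wide-tail cases in the table also sit poorly with the baseline exclusion and with room for 4 losses: the 64% row removes about 7 patients.

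Much of this stands. The loss of long values is a risk, not a certainty, and the upper end of the range is the least plausible. But the 46% row removes only about 4 patients, so a loss of that order fits the allowance. Blinding prevents deliberate selection by arm; it does not prevent selection on the outcome. Nor is this merely detail that an analysis plan would supply: the article itself states the withdrawal ground, the analysis sets and the missing-data rule, and together they conflict with its own outcome list.

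**Conclusion.** The point holds as a selection bias of unknown direction in a secondary outcome. Patients may be removed after randomisation on the expected value of time to extubation, and nothing stated restores them. If the block itself reduces long weans, its benefit is understated. If the complications are unrelated to it, the benefit is unchanged or enlarged. If they are more frequent in the block arm, harm is hidden.

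A reader might infer that the distribution is cut at 24 h in each arm and that any benefit is therefore understated. The document does not support this. It sets no fixed cut, and the named triggers are not ones it says a chest-wall block prevents. Its Discussion links poor pain control to delayed weaning only as general background.

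The size cannot be fixed from the document. The range of about 3% to 64% of the mean difference applies only to proportional shortening, under the assumed medians of 6 to 10 h and log SDs of 0.5 to 1.0 shown above, with every value over 24 h removed. The primary outcome's sample size is not affected by this point.

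**What to change.** Leave the clinical grounds for withdrawal as they are and separate them from data collection:
1. State that withdrawal for these complications does not end collection of extubation time, ICU discharge and length of stay, where consent allows. The consent provision described covers participants who choose to withdraw, so check that it also covers withdrawal by the investigator.
2. Analyse the interval until extubation in all randomised patients by allocated arm, either as time-to-event or by ranks, with the worst rank for patients who die or are never extubated.
3. State that neither a prolonged-intubation exclusion nor LOCF applies to this outcome.

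The cost is wording, possibly as a formal amendment, and retrieval of a few times from the patient file. A few long values will enter the analysis; rank and time-to-event methods handle them. The change should be made before database lock and without knowledge of the arms.
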